### Planned Data Analysis

Acceptability will be determined based on the acceptability Likert scale results as well as the open-ended survey feedback. Open-ended questions will be analyzed via content analysis, and Likert scale acceptability items will be descriptively reported. Feasibility will be assessed based on the completion of the program by individual participants, that is, the ability to recruit into the study and the proportion of participants completing the full program, with feasibility determined by recruiting the minimal sample size and an 80% completion/retention rate [54,55]. Utility will be demonstrated through improvements in subjective distress, mental health symptoms, or resilience between preintervention and postintervention. A paired-sample 2-sided *t* test will be performed for the outcome measures to identify any changes in the outcomes before and after the intervention. Baseline missing data will be removed pairwise, and analyses will be performed using the last observation carried forward.

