## Methods

### Design

This project is an exploratory trial to assess the acceptability, feasibility, and clinical utility of a group-based intervention using a pre-post design with a single group (trial registration ACTRN12624001287527). This protocol is presented in line with SPIRIT (Standard Protocol Items: Recommendations for Interventional Trials) reporting guidelines [43].

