#### Eligibility

##### Inclusion Criteria

Persons aged 10-14 years, of any gender, living in a rural area (defined as areas with a Modified Monash Model 3 or higher, representing large rural towns through to remote communities) with self-reported exposure to one or more natural hazards (eg, fire, flood, tornado, drought) are included in this study. Given that the impacts of hazard exposure can be sustained well past the initial exposure [5,6], there are no time limits on exposure to the hazards. There are no restrictions on participants currently or previously having accessed other mental health interventions.

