### Outcomes

Data will be collected before and after the intervention. The primary assessed outcomes will include changes in the psychological symptoms, resilience, and subjective ratings of distress, with secondary outcomes examining change in climate emotions, from preintervention to postintervention. Acceptability will also be assessed post intervention. Data will be collected by trained independent data collectors.

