#### Psychological Distress

Psychological distress will be assessed using the Depression Anxiety Stress Scale (DASS)-youth version [50], which is a child and adolescent adaptation of the well-validated and widely used DASS-21 [51]. The measure consists of 21 items, with 7 items assessing each of the 3 conditions: depression, anxiety, and stress. Participants are asked to specify the frequency on a 4-point Likert scale (never to almost always), with which they have experienced symptoms. The DASS-youth version has replicated the original factor structure of the DASS-21 and has been validated for use in children aged 7-18 years [50].

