### Limitations

Due to the nature of this pilot study, the sample size is small. This study is also not a randomized controlled trial, and random assignment to groups was not possible. Replication of results in randomized controlled trials with larger samples would be warranted after refinement of the intervention from the pilot. Although the current design is appropriate to gain insight into the effects of the intervention, the research would be strengthened by having longer follow-up times to better assess if the intervention effects are sustained. Outcome measures are child self-report only, and diagnostic interviews or parent reports may also be useful to incorporate into future research designs.

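### Clinical utility is declared demonstrated if any one of three primary domains improves in a single-group pre-post pilot; this claims more than the article's own preliminary framing supports

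*Protocol article*

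**What the plan says.** The Design section describes an exploratory trial "using a pre-post design with a single group". The Outcomes section names several primary outcomes and ranks none above the others: "The primary assessed outcomes will include changes in the psychological symptoms, resilience, and subjective ratings of distress". The Psychological Distress section describes a 21-item DASS, "with 7 items assessing each of the 3 conditions: depression, anxiety, and stress", and does not say whether the total or the subscales will be analysed.

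Planned Data Analysis then sets the rule: "Utility will be demonstrated through improvements in subjective distress, mental health symptoms, or resilience between preintervention and postintervention". The next sentence gives the test: "A paired-sample 2-sided *t* test will be performed for the outcome measures", "to identify any changes in the outcomes before and after the intervention". No minimum improvement is attached to the rule. In the same paragraph, feasibility does get explicit criteria: the minimum sample and 80% completion.

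Elsewhere the claims are more modest. The Sample Size section promises preliminary data on clinical utility, and the Conclusions promise preliminary evidence. Limitations acknowledges the small sample and the lack of randomization, and calls for randomized replication.

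**The concern.** Two features of the rule let it report success when the programme has no effect.

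- **Any-one logic.** Improvement in one domain is enough, so each further score adds another chance of a false positive. One of the routes is a single 0-10 rating of how the child feels at that moment.
- **No comparator.** A pre-post change in one group combines any programme effect with time, expectancy in self-report, regression to the mean and other care. Other care is allowed: "There are no restrictions on participants currently or previously having accessed other mental health interventions". The rule credits all of it as utility.

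At stake is the wording of the conclusion. The Discussion intends the results to guide clinicians treating children. A finding of demonstrated utility would carry more weight with them than this design can support, and more than the article claims for itself elsewhere.

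**Working it through.** **Figure to reproduce.** The article states no error rate or power for the utility rule, so there is none. The two sample sizes used below are its own: the planned minimum of 12 and the 28 children enrolled by March 2025.

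**Inputs from the article.** Three primary domains joined by *or*; three DASS subscales; two-sided paired t tests; one group. The number of scores k is therefore 3 (DASS total, resilience, subjective distress), or 5 if the three subscales are tested separately.

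**Assumptions.** Two-sided alpha 0.05 per test, so 0.025 in the favourable direction; correlation between change scores 0 to 0.5; normal change scores. Correlated cases were simulated with at least 100,000 replicates.

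**Step 1: significance reading, no true change, no drift.** For independent scores the chance of at least one significant improvement is 1 − (1 − 0.025)^k.

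- k=3: 1 − 0.975³ = 7.3%
- k=5: 1 − 0.975⁵ = 11.9%
- Correlation 0.5 (simulated): about 6.4% for k=3 and 9.2-9.5% for k=5
- One score: 2.5%

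**Step 2: direction-only reading, no true change.** For independent scores the chance that at least one mean moves favourably is 1 − 0.5^k.

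- k=3: 1 − 0.5³ = 87.5%
- Correlation 0.5 (simulated): about 75% for k=3

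**Step 3: no programme effect, some untreated change.** The documents give no drift data, so these values are illustrative. Drift is in units of the SD of the change score, with correlation 0.5. Chance of at least one significant improvement:

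| Drift | n=12, k=3 to 5 | n=28, k=3 to 5 |
|---|---|---|
| 0.2 SD | 21-28% | 35-45% |
| 0.3 SD | 33-43% | 58-68% |

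The rate rises with n because a larger sample detects drift more reliably.

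**Step 4: does a multiplicity adjustment cure it?** For an any-one verdict, Holm rejects exactly when Bonferroni does, at 0.05/3 = 0.0167 two-sided for three scores.

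- No drift: the joint rate in the favourable direction returns to about 2.3-2.5%.
- Drift 0.3 SD, k=3, correlation 0.5: the adjusted rule is still met in about 16% of trials at n=12 and 37% at n=28.

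**Step 5: cost in power.** Power of one paired t test for an assumed true change of 0.5 SD of the change score, from the noncentral t with noncentrality 0.5·√n:

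- n=28: 72% at alpha 0.05, 54% at 0.0167
- n=12: 35% at alpha 0.05, 19% at 0.0167

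**The case against.** The strongest defence is that this is a declared pilot. It discloses the missing control arm, lists the small sample, and asks for randomized replication. A single-arm design is not an error in such a study, and alpha, adjustment and the choice between total and subscales are often left to an analysis plan that is not shown. That stands. The absence of a multiplicity method is not itself the point, and the text does not say that the tests will be unadjusted or that the subscales will be tested separately.

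It can also be said that the sentence naming the t test makes significance the natural reading of improvement. That stands too, and on that reading with no drift the inflation is moderate.

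A reader might go further and infer that referral through mental health services and school psychologists guarantees regression to the mean. The documents do not support that. Entry is by age, rurality and hazard exposure, with no distress threshold; recruitment also uses flyers and youth organizations; and no baseline scores are given. Regression to the mean is possible, but its size is unknown.

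A reader might also take the statement in Limitations, "Although the current design is appropriate to gain insight into the effects of the intervention", as a causal claim. The same sentence goes on to say that longer follow-up would strengthen the research, so it is weak evidence of overclaiming.

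What none of this answers is the rule itself. The article, not a later plan, fixes that improvement in any one domain demonstrates utility, and its own cautious framing elsewhere does not qualify that sentence.

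**Conclusion.** The point holds as a defect in the stated rule and its wording. Improvement in one of three primary domains, in one group without a comparator, can support a preliminary signal but cannot demonstrate utility. This is out of step with the exploratory and preliminary framing in Design, Sample Size and Conclusions.

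The size depends on the reading. On the significance reading without drift, the false-success rate is about 6-7% (three scores) or 9-12% (five), against 2.5%. A reader might infer that an inert programme would easily pass. That is true only if improvement means direction alone (about 75-87.5% on three scores), or if there is untreated drift of the order assumed above. Alpha, correlation and drift are all assumptions.

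This should be corrected before results are reported. It does not undermine the pilot's acceptability and feasibility aims, and it is not a fault that must hold up the study.

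**What to change.** In Planned Data Analysis:

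1. Replace the statement that utility will be demonstrated with: *A preliminary signal of utility will be considered present*. Add that pre-post change in a single group cannot be attributed to the intervention.
2. Report the mean change with its 95% CI for every primary outcome, whatever its significance.
3. If a yes/no verdict is kept, define improvement as a significant change in the favourable direction on one prespecified score per domain. Then either apply Holm across the three scores or print the joint error rate (about 6-7% under the assumptions above) beside the verdict.

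Items 1 and 2 cost only a softer conclusion, and they can be made with children already enrolled because no data collection changes. Holm in item 3 has a real price: for an assumed 0.5 SD change, power per outcome at the first Holm step falls from 72% to 54% at n=28 and from 35% to 19% at n=12. Stating the joint error rate instead is therefore a reasonable choice for a pilot. Item 1 is needed either way, since no adjustment separates drift from effect. Splitting the results by concurrent mental health care is not recommended, because with 12 to 28 children it would tell little.

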#### Intervention Overview

The Bee Well intervention is informed by the resilience-building empirical evidence, alongside emerging evidence surrounding coping with climate change [37,38], which also points to the value of ecotherapy, nature connectedness, and nature immersion [40]. The intervention is designed to be run in a group setting in order to normalize climate change–related emotions and foster social support [31]. The intervention takes place predominantly outdoors to enable nature exposure and connection and consists of guided discussion and activities that focus on providing psychoeducation on emotional awareness and climate emotions, developing adaptive coping strategies for coping with climate change distress and hazards, and building resilience (see Table 1). The intervention also includes a nature restoration–based activity, occurring alongside discussions around meaning-making and coping, in order to foster efficacy and engage in shared action. Group members have their own individual workbooks and complete a range of individual and group activities, in addition to the nature restoration task. The intervention consists of 5 modules, with each module lasting approximately 60 minutes and will be co-delivered by a team of provisional and clinical psychologists with an interest in child and adolescent mental health, rural health, and/or eco-anxiety.

**Table 1 table1:** Intervention modules.

Module	Description	Purpose
Module 1: Finding Common Ground	In this module, individuals explore and share their own eco-emotions, including grief, worry, and hope, through 2 interactive group activities (exploring eco-emotions and exploring mixed feelings).	Psychoeducation regarding emotions; build emotional awareness, recognition of shared experiences, and enable group processing
Module 2: Taking Action Together	In this module, the group commences a shared nature restoration activity—flora-based or fauna-based—such as building bee hives. While engaging in the activity, the group also undertakes guided discussions regarding “taking action” and exploring their own relationships with nature.	Taking action together through engaging in nature restoration as a form of coping and building group-efficacy and a means to support meaning making and fostering peer connection

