Module 3: Coping	In this module, the group is introduced to coping skills through activities and group discussions. Group members undertake a mindfulness nature meditation/journaling task as a means of connecting with nature and rewilding.	Build adaptive coping skills, including promoting nature connectedness as a means of coping, and fostering resilience
Module 4: Cultivating Resilience	In this module, the group completes the nature restoration activity. Further discussions focus on fostering resilience and developing individual coping and resilience plans.	Build sense of community, group-efficacy, and self-efficacy; build resilience
Module 5: Bringing It Together	In this module, the group reflects on the nature restoration activity and discusses how this project will restore nature into the future. This module also includes a final reflection on the learnings and outlines avenues for ongoing or future support.	Reflection on the intervention and learnings

The Bee Well intervention resources can be found in the publicly available manual and workbook [47,49]. The intervention delivery is provided by trained psychologists who are able to manage referral or escalation, as needed, should any distress arise from or during participation. Information on referral sources is also provided to parents as part of the information sheet.

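### The paired t test treats children's changes as independent although the intervention is delivered in groups, so p-values may be too small if changes correlate within a group

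*Protocol article*

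**What the plan says.** The design is single-arm: it is described as "using a pre-post design with a single group". The only inferential method named under Planned Data Analysis is "A paired-sample 2-sided" *t* "test will be performed for the outcome measures". The same section ties clinical utility to improvement in subjective distress, mental health symptoms or resilience.

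On delivery, Intervention Overview states: "The intervention is designed to be run in a group setting in order to normalize climate change–related emotions and foster social support". The modules "will be co-delivered by a team of provisional and clinical psychologists". Table 1 gives the purpose of Module 4 as "Build sense of community, group-efficacy, and self-efficacy; build resilience". Its other modules include a joint nature restoration task and guided group discussion.

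The article does not mention delivery group in the analysis, an ICC, or the number and size of groups. The Limitations section names the small sample and the lack of randomization, but not clustering.

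**The concern.** Pairing removes correlation between a child's two measurements. It does nothing about correlation between children. The article's own rationale expects some of the benefit to arise at group level, so children who share a restoration task, discussions and sessions may change together. If they do, 28 children carry less information than 28 independent changes, and the t test does not allow for it.

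At stake is the stated precision of the changes in symptoms, resilience and distress, which are the primary outcomes and the basis for calling the intervention useful. The results are meant to inform practitioners, so overstated precision would matter even in a pilot.

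**Working it through.** **Inputs from the article.** Two-sided paired t test (Planned Data Analysis); group delivery (Intervention Overview and Table 1); 28 children enrolled as of March 2025 (Results).

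**Assumed, because not stated.** Nominal significance level 5%; 28 analysed children in 4 groups of 7 or 2 groups of 14; ICC of the change scores from 0 to 0.10.

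**Step 1: the plan's own figure.** The only sample-size figure is the minimum of 12. It reproduces as 10 × 1.2 = 12 (10/0.8 = 12.5 would round up to 13). It rests on no test or power claim, so this point leaves it unchanged.

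**Step 2: which correlation matters.** Write the change of child i in group j as δ + u_j + e_ij, with ICC = var(u)/[var(u) + var(e)]. A stable difference in level between groups cancels in the paired change. Only group-level variation in *change* counts.

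**Step 3: design effect.** The variance of the mean change is (σ²/N) × DEFF, with DEFF = 1 + (m − 1) × ICC for equal groups of size m. The t test in effect sets DEFF to 1. The SE should be multiplied by √DEFF, and the effective n is N/DEFF.

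**Step 4: type I error.** Changes were simulated with true mean zero, a normal group effect with variance ICC and a normal child effect with variance 1 − ICC. They were tested with the ordinary t test on 27 degrees of freedom, with 40,000 or more runs per scenario.

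| Groups | ICC | DEFF | √DEFF | Effective n | Type I error |
|---|---|---|---|---|---|
| 4 × 7 | 0 | 1.00 | 1.00 | 28.0 | about 5% |
| 4 × 7 | 0.02 | 1 + 6 × 0.02 = 1.12 | 1.06 | 25.0 | about 6.3% |
| 4 × 7 | 0.05 | 1 + 6 × 0.05 = 1.30 | 1.14 | 21.5 | about 8.5% |
| 4 × 7 | 0.10 | 1 + 6 × 0.10 = 1.60 | 1.26 | 17.5 | about 12% |
| 2 × 14 | 0 | 1.00 | 1.00 | 28.0 | about 5% |
| 2 × 14 | 0.02 | 1 + 13 × 0.02 = 1.26 | 1.12 | 22.2 | about 8% |
| 2 × 14 | 0.05 | 1 + 13 × 0.05 = 1.65 | 1.28 | 17.0 | about 12.6% |
| 2 × 14 | 0.10 | 1 + 13 × 0.10 = 2.30 | 1.52 | 12.2 | about 20% |

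At the minimum sample of 12 in 2 groups of 6, the error is about 7.5% and 10.7% at ICC 0.05 and 0.10. If all 12 formed one group it would be about 11% and 18%, and the data could not reveal it.

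**Step 5: mean and SD.** Clustering of this kind does not bias the mean change. The expected sample variance is σ² × [1 − (m − 1) × ICC/(N − 1)]. For 4 × 7 at ICC 0.10 this is 1 − 0.6/27 = 0.978, so the SD is about 1.1% low. For 2 × 14 at ICC 0.10 it is 1 − 1.3/27 = 0.952, so the SD is about 2.4% low.

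**Step 6: price of a full group-level test.** With 4 groups it has 3 degrees of freedom: 3.18/2.05 = 1.55 times the width even at ICC 0, and 1.55 × 1.14 = 1.77 times at ICC 0.05. With 2 groups it has 1 degree of freedom: 12.71/2.05, over 6 times the width.

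**The case against.** The strongest reply is that the harm is conditional and the stakes are low. Group number, group size, ICC and significance level are all assumed; at ICC 0 nothing is wrong and at 0.01 the effect is small. This is an exploratory single-arm pilot without a power claim. Feasibility rests on recruitment and 80% completion, and acceptability is descriptive, so neither is affected. Utility is defined by improvement with no p-value threshold attached, and no confidence intervals are announced. An article may also leave group structure and sensitivity analyses to a fuller document.

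Most of that stands and limits the point. It does not remove it: the test is named, so independence between children is a choice the article has fixed, and its own account of the mechanism makes that assumption doubtful.

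Three stronger readings are tempting and not supported:

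- *The standard errors are too small for every primary outcome.* The article contains nothing that shows a positive ICC for any outcome.
- *SDs and effect sizes carried into a later trial would be distorted.* Step 5 shows the SD barely moves, and the article does not say its estimates will size a later trial; Limitations says only that larger randomized replication would be warranted.
- *Shared facilitators are a source of clustering.* A team co-delivers, but allocation of facilitators to groups is not described. If the same team ran every group, facilitators would add no between-group variation. Individual workbooks and coping plans are also part of the intervention.

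Nor does the design's wording about a single group mean one delivery cohort. It describes the absence of a comparator.

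**Conclusion.** The point holds in conditional form. The named analysis ignores delivery group in an intervention designed to act partly through the group. If changes correlate within groups, p-values for the utility outcomes, and any intervals built from the same SEs, will overstate precision. Under the stated assumptions a nominal 5% test runs at about 6% to 12% with 4 groups of 7, and about 8% to 20% with 2 groups of 14, for ICC 0.02 to 0.10. The true size cannot be derived from the article. Sample size, feasibility and acceptability are not affected. It is worth correcting because the correction is cheap, but it does not undermine the pilot.

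**What to change.** Record each child's delivery group. Report the number and size of groups and the mean change by group. Present each t-test result beside a version with the SE multiplied by √(1 + (m − 1) × ICC) for ICC 0.05 and 0.10; with unequal groups, replace m by Σmⱼ²/N. State the significance level.

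Use a random intercept for group with small-sample degrees of freedom only if there are enough groups to estimate it. If all children fall into one or two groups, say that the group effect cannot be separated from the intervention effect (one group) or reliably estimated apart from it (two groups), and treat the p-values as descriptive.

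The cost is one identifier and a few lines of text. The article mentions only a unique code per child, so whether delivery group is already on file is not stated. Under the SE inflation, intervals widen by about 14% to 26% for 4 groups of 7 and 28% to 52% for 2 groups of 14. A group-level test with so few groups would widen them far more (Step 6), which is why it should not be the default.

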### Participants

#### Sample Size

Being an intervention pilot precludes definitive sample size calculation [44]. However, it has been argued that, for clinical intervention pilots, a minimum of 10 samples in the intervention group is required [45]. In order to allow for up to 20% attrition and ensure sufficient data for preliminary efficacy testing, a minimum sample of 12 is anticipated, which is sufficient to provide acceptability and feasibility data and preliminary data regarding clinical utility [44].

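### With one pre and one post score, last observation carried forward records a change of exactly zero for each child without a post score, which distorts the size and precision of the reported change

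*Protocol article*

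**What the plan says.** The Design section describes a study "using a pre-post design with a single group". On timing, the Outcomes section says "Data will be collected before and after the intervention"; the article describes no interim or later outcome assessment. The primary outcomes are the changes in psychological symptoms, resilience and subjective distress.

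Under Planned Data Analysis, "A paired-sample 2-sided *t* test will be performed for the outcome measures", and improvement in distress, symptoms or resilience is what demonstrates utility. The missing-data rule in the same section is "Baseline missing data will be removed pairwise, and analyses will be performed using the last observation carried forward".

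On expected loss, the Sample Size section sets its minimum "In order to allow for up to 20% attrition", and Planned Data Analysis makes "an 80% completion/retention rate" part of the feasibility criterion. The Results section reports 28 children enrolled as of March 2025.

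**The concern.** Children with a missing baseline are removed, so LOCF can act only on a child who has a baseline and no post score. That child has one earlier observation, the baseline itself. Copying it into the post column produces a difference of exactly zero, which enters the paired analysis as if it had been measured.

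This has two effects. The mean change is mixed with zeros that nobody observed. The zeros also reduce the spread of the changes and raise the count, so the standard error falls although no information has been added. The change scores carry the utility claim, and in a pilot their size and SD are the main quantitative result on utility. The article chooses this method outright, so the point is not about detail left to a fuller document.

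**Working it through.** **Inputs from the protocol article.** One pre and one post score (Outcomes); paired two-sided t test and LOCF (Planned Data Analysis); required minimum 10, attrition allowance up to 20%, planned minimum 12 (Sample Size); 28 enrolled (Results).

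**Assumptions.** The article gives no effect size, SD of change or alpha. I take alpha 0.05, normal changes with SD s = 1, and positive values for improvement. Effects are in SD units.

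**The plan's own figure.** 10 × (1 + 0.20) = 12, which reproduces the stated minimum. Dividing instead gives 10 / 0.80 = 12.5, or 13. The difference is of no consequence with 28 enrolled.

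**Mean.** Let p be the share with a post score, d the mean change in those children, and m the true mean change in the children without one.
- True mean = p·d + (1 − p)·m
- LOCF mean = p·d, so its bias is −(1 − p)·m
- Observed-pairs mean = d, so its bias is (1 − p)·(d − m)

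LOCF is unbiased only if m = 0. It is too low if m > 0 and too high if m < 0.

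**Standard error.** The variance of the LOCF changes is about p·s² + p(1 − p)·d². Hence SE(LOCF) / SE(observed pairs) ≈ p·√(1 + (1 − p)(d/s)²).

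**28 children, 6 missing, d = m = 0.5.** p = 22/28 = 0.786.
- LOCF mean: 0.786 × 0.5 = 0.393, against a true 0.500.
- LOCF SE: √((0.786 + 0.786 × 0.214 × 0.25)/28) = √(0.828/28) = 0.172; simulated 0.170.
- Observed-pairs SE: 1/√22 = 0.213; simulated 0.211.
- With all 28 measured: 1/√28 = 0.189, so the LOCF SE (0.170/0.189 = 0.90) is about 10% below even complete data.

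**Simulation** (at least 50,000 runs per scenario, nominal 95% t intervals, children without a post score changing as much as the others):

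| Children | Missing | d | LOCF mean | LOCF coverage | Observed-pairs coverage |
|---|---|---|---|---|---|
| 12 | 2 | 0.5 | 0.42 | 94.1% | 94.9% |
| 28 | 5 | 0.5 | 0.41 | 92% | 95% |
| 28 | 6 | 0.5 | 0.39 | 90.5% | 95% |
| 28 | 6 | 0.8 | 0.63 | 85% | 95% |

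The 0.41 is 23/28 × 0.5. In the third row the mean interval width is 0.70 for LOCF and 0.88 for observed pairs, a ratio of 0.80.

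**Where the coverage goes.** The LOCF estimate itself scatters with SD 0.786 × 0.213 = 0.168, close to its reported SE. Coverage is lost because a shifted estimate is paired with an SE that leaves no room for not knowing what happened to the unmeasured children.

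**Range of effects.** The SE ratio reaches 1 at d/s = √((1/p² − 1)/(1 − p)). That is 1.62 for p = 10/12, 1.68 for p = 0.80 and 1.70 for p = 22/28. Below about 1.6 SD the LOCF interval is narrower than the observed-pairs interval; above about 1.7 SD it is wider.

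**Worsening case.** With 22 children at +0.5 and 6 at −0.5, the true mean is (11 − 3)/28 = 0.286. LOCF reports 11/28 = 0.393 (coverage 92%); observed pairs report 0.500 (coverage 84%).

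**Test.** If nobody changes, the t test with LOCF rejects in 4.8% to 5.0% of runs. Power at d = 0.5 is about 60% with either method for 28 children with 6 missing, and about 29% to 30% for 12 with 2 missing.

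**The case against.** The best defence of LOCF is the worsening case. There its error is 0.393 − 0.286 = 0.107, and that of observed pairs is 0.214, twice as large. From the bias formulas, LOCF is the less biased of the two whenever children without a post score improved by less than half as much as the others (m < d/2). A mixed model on the same scores assumes that observed data explain the missingness, so it does not repair this case either. This stands, and it is why switching to observed pairs alone is not enough.

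Second, the planned inference is a t test and the article mentions no confidence interval. The test's level and power are nearly untouched. That also stands. A reader might infer that LOCF makes the utility test invalid; the calculations do not support this. The harm is to the estimate and to the SE that any interval would use.

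Third, 20% is a ceiling that the plan allows for, not a rate that it predicts. Six of 28 (21.4%) leaves 78.6%, which would miss the 80% criterion if all six count as not retained. With five of 28 or two of 12 missing, the damage is smaller, as the table shows. If nobody lacks a post score, there is none.

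**Conclusion.** The point holds: in this design LOCF is baseline carried forward, and it treats an assumption of no change as data. With 5 or 6 of 28 post scores missing and an assumed 0.5 SD change in everyone, the reported change is 18% to 21% too small (5/28 and 6/28), and interval coverage falls to 92% or 90.5%. With 2 of 12 missing, coverage is about 94%. These sizes rest on the assumed effect and on unmeasured children changing like the rest. The direction of bias depends on their actual course.

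Four stronger readings are tempting, and the documents do not support them:
- That LOCF is always wrong, or always conservative. It is right if those children did not change, and too favourable if they worsened.
- That its interval is too narrow at every effect size. It is not above about 1.7 SD.
- That every child who leaves the programme is affected. A child who stops attending but completes the post measures is not.
- That a later trial would be sized on these figures. The Limitations section says only that randomized replication would be warranted.

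Severity: should-fix.

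**What to change.** Drop LOCF as the primary method. Analyse all available pre and post scores with a likelihood-based mixed model (time fixed, child random), or use observed pairs. Report how many children lack a post score. Add a sensitivity analysis in which those children are assumed unchanged and then worsened, because both the mixed model and observed pairs overstate benefit if they worsened. LOCF may remain only as the labelled no-change version of that analysis.

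The cost is a sentence or two in the analysis section, a few lines of code and no new data. Intervals become wider, by up to about 25% in the case worked above (0.88/0.70 ≈ 1.25).
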